#### **Concerning the SCBT,**

What are your current **expectations of the effectiveness** of the SCBT (effectiveness may relate to more than one objective, you may wish to detail/nuance)? Have these expectations changed since the beginning of TreatPaCS? If yes, please specify.

What are your current impressions of the **ease of implementation** of the SCBT? Have these impressions changed since the beginning of TreatPaCS? If so, please explain.

What is your current judgement of the **objectives and aspects worked** on by the SCBT? Has this judgement changed since the beginning of TreatPaCS? If so, please specify.

What are your current impressions of the **adaptability** of the SCBT to each child? Have these impressions changed since the beginning of TreatPaCS? If so, please explain.

What are your current impressions of the **investment** required of the parent and the SLT in the SCBT? Have these impressions changed since the beginning of TreatPaCS? If so, please explain.

Is there any aspect of the SCBT that you **particularly appreciate** at present? If yes, please specify. Have there been any changes in this area since the start of TreatPaCS?

Is there any aspect of the SCBT that you **currently dislike**? If yes, please specify. Have there been any changes in this area since the start of TreatPaCS?

What do you think of the **documents accompanying** the SCBT (manual, checklists, others)? Do you find them sufficiently helpful and detailed? Please specify.

**Did your participation in this study lead to any changes in your professional practice? If so, please specify.**

## Le point de vue des cliniciens impliqués dans l'étude TreatPaCS

**Nom, prénom :**

Nombre d'années d'expérience dans la prise en charge des enfants d'âge préscolaire qui bégayaient :

Nombre d'années d'expérience dans la mise en place du programme Lidcombe :

Nombre d'années d'expérience dans la mise en place du programme Mini-KIDS :

Nombre d'années d'expérience dans la mise en place de la thérapie sociale-cognitive :

**Avez-vous actuellement une préférence pour un des trois programmes ? Si oui, pouvez-vous détailler ce qui explique actuellement cette préférence ?**

**Par rapport au programme Lidcombe,**

Quelles sont vos attentes actuelles quant à l'efficacité du Programme Lidcombe (l'efficacité peut porter sur plusieurs objectifs, vous pouvez détailler/nuancer) ? Ces attentes ont-elles changé depuis le début de TreatPaCS ? Si oui, précisez.

Quelles sont vos impressions actuelles par rapport à la facilité de mise en œuvre du Programme Lidcombe ? Ces impressions ont-elles changé depuis le début de TreatPaCS ? Si oui, précisez.

Quelle est votre appréciation actuelle des objectifs visés et des aspects travaillés par le Programme Lidcombe ? Cette appréciation a-t-elle changé depuis le début de TreatPaCS ? Si oui, précisez.

Quelles sont vos impressions actuelles par rapport au caractère adaptable du Programme Lidcombe à chaque patient ? Ces impressions ont-elles changé depuis le début de TreatPaCS ? Si oui, précisez.

Quelles sont vos impressions actuelles par rapport à l'investissement demandé dans le Programme Lidcombe pour le parent et la logopède ? Ces impressions ont-elles changé depuis le début de TreatPaCS ? Si oui, précisez.

Y a-t-il un aspect du Programme Lidcombe que vous appréciez spécialement, actuellement ? Si oui, veuillez préciser. Y a-t-il eu des changements à ce niveau depuis le début de TreatPaCS ?

Y a-t-il un aspect de du Programme Lidcombe que vous aimez moins, actuellement ? Si oui, veuillez préciser. Y a-t-il eu des changements à ce niveau depuis le début de TreatPaCS ?

Que pensez-vous des documents accompagnant le Programme Lidcombe (manuel, checklists, autres) ? Vous semblent-ils suffisamment aidant et détaillés ? Veuillez préciser.

#### **Par rapport au programme Mini-KIDS**

Quelles sont vos attentes actuelles par rapport à l'efficacité du programme Mini-KIDS (l'efficacité peut porter sur plusieurs objectifs, vous pouvez détailler/nuancer) ? Ces attentes ont-elles changé depuis le début de TreatPaCS ? Si oui, précisez.

Quelles sont vos impressions actuelles par rapport à la facilité de mise en œuvre du programme Mini-KIDS ? Ces impressions ont-elles changé depuis le début de TreatPaCS ? Si oui, précisez.

Quelle est votre appréciation actuelle des objectifs visés et des aspects travaillés par le programme Mini-KIDS ? Cette appréciation a-t-elle changé depuis le début de l TreatPaCS ? Si oui, précisez.

Quelles sont vos impressions actuelles par rapport au caractère adaptable du programme Mini-KIDS à chaque patient ? Ces impressions ont-elles changé depuis le début de l TreatPaCS ? Si oui, précisez.

Quelles sont vos impressions actuelles par rapport à l'investissement demandé dans le programme Mini-KIDS pour le parent et la logopède ? Ces impressions ont-elles changé depuis le début de TreatPaCS ? Si oui, précisez.

Y a-t-il un aspect du programme Mini-KIDS que vous appréciez spécialement, actuellement ? Si oui, veuillez préciser. Y a-t-il eu des changements à ce niveau depuis le début de TreatPaCS ?

Y a-t-il un aspect du programme Mini-KIDS que vous aimez moins, actuellement ? Si oui, veuillez préciser. Y a-t-il eu des changements à ce niveau depuis le début de TreatPaCS ?

Que pensez-vous des documents accompagnant le programme Mini-KIDS (manuel, checklists, autres) ? Vous semblent-ils suffisamment aidant et détaillés ? Veuillez préciser.

### **Par rapport à la thérapie sociale-cognitive**

Quelles sont vos attentes actuelles par rapport à l'efficacité de la thérapie sociale-cognitive (l'efficacité peut porter sur plusieurs objectifs, vous pouvez détailler/nuancer) ? Ces attentes ont-elles changé depuis le début de TreatPaCS ? Si oui, précisez.

Quelles sont vos impressions actuelles par rapport à la facilité de mise en œuvre de la thérapie sociale-cognitive ? Ces impressions ont-elles changé depuis le début de TreatPaCS ? Si oui, précisez.

Quelle est votre appréciation actuelle des objectifs visés et des aspects travaillés par la thérapie sociale-cognitive ? Cette appréciation a-t-elle changé depuis le début de TreatPaCS ? Si oui, précisez.

Quelles sont vos impressions actuelles par rapport au caractère adaptable de la thérapie sociale-cognitive à chaque patient ? Ces impressions ont-elles changé depuis le début de TreatPaCS ? Si oui, précisez.

Quelles sont vos impressions actuelles par rapport à l'investissement demandé dans la thérapie sociale-cognitive pour le parent et la logopède ? Ces impressions ont-elles changé depuis le début de TreatPaCS ? Si oui, précisez.

Y a-t-il un aspect de la thérapie sociale-cognitive que vous appréciez spécialement, actuellement ? Si oui, veuillez préciser. Y a-t-il eu des changements à ce niveau depuis le début de TreatPaCS ?

Y a-t-il un aspect de la thérapie sociale-cognitive que vous aimez moins, actuellement ? Si oui, veuillez préciser. Y a-t-il eu des changements à ce niveau depuis le début de TreatPaCS ?

Que pensez-vous des documents accompagnant la thérapie sociale-cognitive (manuel, checklists, autres) ? Vous semblent-ils suffisamment aidant et détaillés ? Veuillez préciser.

Votre participation à cette étude a-t-elle amené des changements dans votre pratique professionnelle ? Si oui, veuillez spécifier.

## Perspectief van logopedisten betrokken in de TreatPaCS-studie

### Familienaam, voornaam:

Ervaringen met het behandelen van kleuters die stotteren (in jaren ervaring) :

Ervaringen met het Lidcombe Programma (in jaren ervaring) :

Ervaringen met Mini-KIDS (in jaren ervaring) :

Ervaringen met de sociaal-cognitieve gedragstherapie (in jaren ervaring) :

Heb je momenteel een voorkeur voor één van de drie behandelingen? Indien ja, kan je uitleggen wat deze voorkeur momenteel inhoudt?

### Over het Lidcombe Programma,

Wat zijn je verwachtingen op dit moment over de effectiviteit van het Lidcombe Programma (effectiviteit houdt mogelijks meer dan één doel in, specificeer/nuanceer gerust)? Zijn je verwachtingen veranderd sinds de start van TreatPaCS? Indien ja, wil je uitleggen waarom?

Hoe moeilijk of gemakkelijk denk je op dit moment dat het Lidcombe Programma kan worden geïmplementeerd? Denk je hier anders over sinds de start van TreatPaCS? Indien ja, wil je uitleggen waarom?

Wat denk je op dit moment over de doelen en aspecten waarop gewerkt wordt in het Lidcombe Programma? Denk je hier anders over sinds de start van TreatPaCS? Indien ja, wil je uitleggen waarom?

Wat denk je op dit moment over de mogelijkheid om het Lidcombe Programma aan te passen aan elke kleuter die je behandelt? Denk je hier anders over sinds de start van TreatPaCS? Indien ja, wil je uitleggen waarom?

Wat denk je op dit moment over de betrokkenheid die in het Lidcombe Programma gevraagd wordt aan de ouder en de logopedist? Denk je hier anders over sinds de start van TreatPaCS? Indien ja, wil je uitleggen waarom?

Is er een aspect in het Lidcombe Programma dat je op dit moment bijzonder waardeert? Indien ja, wil je uitleggen waarom? Denk je hier anders over sinds de start van TreatPaCS? Indien ja, wil je uitleggen waarom?

Is er een aspect in het Lidcombe Programma dat je op dit moment helemaal niet waardeert? Indien ja, wil je uitleggen waarom? Denk je hier anders over sinds de start van TreatPaCS? Indien ja, wil je uitleggen waarom?

Hoe vind je de documenten die voor het Lidcombe Programma beschikbaar zijn (handleiding, checklijsten, andere)?  
Vind je ze voldoende behulpzaam en gedetailleerd? Kan je dit uitleggen?

**Over Mini-KIDS,**

Wat zijn je verwachtingen op dit moment over de effectiviteit van Mini-KIDS (effectiviteit houdt mogelijks meer dan één doel in, specificeer/nuanceer gerust)? Zijn je verwachtingen veranderd sinds de start van TreatPaCS? Indien ja, wil je uitleggen waarom?

Hoe moeilijk of gemakkelijk denk je op dit moment dat Mini-KIDS kan worden geïmplementeerd? Denk je hier anders over sinds de start van TreatPaCS? Indien ja, wil je uitleggen waarom?

Wat denk je op dit moment over de doelen en aspecten waarop gewerkt wordt in Mini-KIDS? Denk je hier anders over sinds de start van TreatPaCS? Indien ja, wil je uitleggen waarom?

Wat denk je op dit moment over de mogelijkheid om Mini-KIDS aan te passen aan elke kleuter die je behandelt? Denk je hier anders over sinds de start van TreatPaCS? Indien ja, wil je uitleggen waarom?

Wat denk je op dit moment over de betrokkenheid die in Mini-KIDS gevraagd wordt aan de ouder en de logopedist? Denk je hier anders over sinds de start van TreatPaCS? Indien ja, wil je uitleggen waarom?

Is er een aspect in Mini-KIDS dat je op dit moment bijzonder waardeert? Indien ja, wil je uitleggen waarom? Denk je hier anders over sinds de start van TreatPaCS? Indien ja, wil je uitleggen waarom?

Is er een aspect in Mini-KIDS dat je op dit moment helemaal niet waardeert? Indien ja, wil je uitleggen waarom? Denk je hier anders over sinds de start van TreatPaCS? Indien ja, wil je uitleggen waarom?

Hoe vind je de documenten die voor Mini-KIDS beschikbaar zijn (handleiding, checklijsten, andere)? Vind je ze voldoende behulpzaam en gedetailleerd? Kan je dit uitleggen?

Wat zijn je verwachtingen op dit moment over de effectiviteit van de sociale cognitieve gedragstherapie (effectiviteit houdt mogelijks meer dan één doel in, specificeer/nuanceer gerust)? Zijn je verwachtingen veranderd sinds de start van TreatPaCS? Indien ja, wil je uitleggen waarom?

Hoe moeilijk of gemakkelijk denk je op dit moment dat de sociale cognitieve gedragstherapie kan worden geïmplementeerd? Denk je hier anders over sinds de start van TreatPaCS? Indien ja, wil je uitleggen waarom?

Wat denk je op dit moment over de doelen en aspecten waarop gewerkt wordt in de sociale cognitieve gedragstherapie? Denk je hier anders over sinds de start van TreatPaCS? Indien ja, wil je uitleggen waarom?

Wat denk je op dit moment over de mogelijkheid om de sociale cognitieve gedragstherapie aan te passen aan elke kleuter die je behandelt? Denk je hier anders over sinds de start van TreatPaCS? Indien ja, wil je uitleggen waarom?

Wat denk je op dit moment over de betrokkenheid die in h de sociale cognitieve gedragstherapie gevraagd wordt aan de ouder en de logopedist? Denk je hier anders over sinds de start van TreatPaCS? Indien ja, wil je uitleggen waarom?

Is er een aspect van de sociale cognitieve gedragstherapie dat je op dit moment bijzonder waardeert? Indien ja, wil je uitleggen waarom? Denk je hier anders over sinds de start van TreatPaCS? Indien ja, wil je uitleggen waarom?

Is er een aspect van de sociale cognitieve gedragstherapie dat je op dit moment helemaal niet waardeert? Indien ja, wil je uitleggen waarom? Denk je hier anders over sinds de start van TreatPaCS? Indien ja, wil je uitleggen waarom?

Hoe vind je de de documenten die voor de sociale cognitieve gedragstherapie beschikbaar zijn (handleiding, checklijsten, andere)? Vind je ze voldoende behulpzaam en gedetailleerd? Kan je dit uitleggen?

Leidde je deelname aan TreatPaCS tot veranderingen in je professionele aanpak? Indien ja, wil je dit uitleggen?

## APPENDIX 3. ANAMNESIS FORM

English/French/Dutch version

Underlined text is to be uploaded to the REDCap system.

**(I/E) = Inclusion/Exclusion criterion (also uploaded to REDCap)**

### IDENTIFICATION CHILD/IDENTIFICATION ENFANT/IDENTIFICATIE KIND

Full name/Nom et prénom/Volledige naam:

Gender child/Sexe de l'enfant/Geslacht van het kind:

Dat of birth of child/Date de naissance de l'enfant/Geboortedatum van het kind:

**(I/E) Age of child at this time (= the time of informed consent signature)/Age de l'enfant à ce moment (= moment de la signature du consentement éclairé)/Leeftijd van het kind op dit moment (= het moment waarop het informed consent getekend wordt): ... Y (Number of years/ Nombre d'années/ Aantal jaren) .... (Number of months/ Nombre de mois/ Aantal maanden)**

Travel time to the SLT/ Temps de déplacement chez la logopède/ Reistijd naar logopedist:

- 0-5 minutes
- 6-10 minutes
- 11-15 minutes
- 16-20 minutes
- 21-25 minutes
- 26 – 30 minutes
- > 30 minutes (please specify)

### FAMILY CIRCUMSTANCES/CONDITIONS FAMILIALES/FAMILIALE OMSTANDIGHEDEN

Do the parents live together? Les parents vivent-ils ensemble? Wonen de ouders samen?

Yes/no Oui/non Ja/nee

Parents are married/ Parents sont mariés/ Ouders zijn getrouwd

Parents are living together/ Parents sont co-habitants/ Ouders zijn samenwonend

Parents are divorced/ Parents sont divorcés/ Ouders zijn gescheiden

Other/ Autre/ Ander:

Extra information/Commentaires/Extra informatie:

Does the child have siblings? / L'enfant, a-t-il des frères-soeurs? / Heeft het kind broers-zussen?

Yes/no/ Oui/non/ Ja/nee,

How many?/Combien?/Hoeveel?

Age for each brother/Age pour chaque frère /Leeftijd voor elke broer:

1. ....
2. ....
3. ....
- 4.

Age for each sister/Age pour chaque soeur /Leeftijd voor elke zus:

1. ....
2. ....
3. ....
- 4.

## DESCRIPTION OF STUTTERING BEHAVIOUR/DESCRIPTION DU BÉGAIEMENT/BESCHRIJVING VAN HET STOTTEREN

Description (by the parent) of the stuttering behaviour at home and at school at this moment- short summary):.....

Description (par le parent) du bégaiement à la maison et à l'école maintenant -: court résumé: .....

Beschrijving (door de ouder) van het stottergedrag thuis en op school op dit moment - / korte samenvatting: .....

Identified (by SLT) overt stuttering behaviour/ Identifié (par la logopède) comportements de bégaiement observables/Overt stottergedrag (geïdentificeerd door de logopedist)

More than one can apply/ Plus qu'une peut être présent/ Meer dan één kan aanwezig zijn:

- Repetitions (syllable, incomplete syllable repetition, multisyllable unit repetition)  
Répétitions (syllabe, syllabes incomplètes, répétitions de plusieurs syllabes)  
Herhalingen (lettergreep, onvolledige lettergreepherhaling, multisyllabische deelherhaling)  
*Ask for examples/Demander des exemples/Vraag naar een voorbeeld:*
- 'Fixed postures' (audible prolongations, prolongations without audible airflow, blocks)  
'Postures fixes' (prolongations audibles, prolongations silencieuses, blocages)  
'Fixed postures' (hoorbare verlengingen, niet hoorbare verlengingen, blokkades)  
*Ask for examples/Demander des exemples/Vraag naar een voorbeeld:*
- Reactive behaviour/Comportement associés/Reactief gedrag:
- Tension/Tension/Spanning (Where, how? /Où, comment? /Waar, hoe?):
- Other fighting behaviour/Autre comportement de forçage/Ander vechtgedrag:
- Avoiding behaviour/Comportement d'évitement/Vermijdingsgedrag:
- Other observable behaviour (Start behaviour, postponing behaviour, other):  
Autre comportement observable pour aider au démarrage des mots, pour retarder la prononciation d'un mot, etc.):  
Ander observeerbaar gedrag (startgedrag, uitstelgedrag, ander):

Identified (by SLT) covert stuttering behaviour/ Identifié (par la logopède) comportements non observables/ Covert stottergedrag (geïdentificeerd door de logopedist):

- Non-verbal signs/Signes non-verbaux/Non verbale tekenen:
- Verbal signs (Child formulated a concern)/ Signes verbaux (L'enfant formulait une préoccupation./ Verbale tekenen (Kind formuleerde een probleem). Explain/Expliquez/Leg uit: .....

How would you (parent) rate the child's stuttering severity today? / Comment évalues-tu (parent) la gravité du bégaiement de l'enfant aujourd'hui ? / Hoe zou u (ouder) de stotterernst van je kind vandaag beoordelen?

Please put the slider on the line for your child's stuttering severity today with 0 = no stuttering, 1 = extremely mild stuttering and 9 = extremely severe stuttering. / Veuillez mettre le curseur sur la ligne à l'endroit correspondant à la sévérité du bégaiement de votre enfant aujourd'hui avec la sévérité de 0 = pas de bégaiement, 1 = extrêmement léger et 9 = extrêmement grave. / Zet de slider alstublieft op de lijn voor de stotterernst van uw kind vandaag met 0 = geen stotteren, 1 = extreem mild stotteren en 9 = extreem ernstig stotteren.

|                  |                                 |                                   |
|------------------|---------------------------------|-----------------------------------|
| No
stuttering | Extremely
mild
stuttering | Extremely
severe
stuttering |
|------------------|---------------------------------|-----------------------------------|

How satisfied are you (parent) with your child's communication in everyday speaking situations at the present time?

/ Dans quelle mesure es-tu (parent) satisfait de la communication de ton enfant dans les situations d'expression quotidienne à ce moment-ci? / Hoe tevreden bent u (ouder) met de communicatie van uw kind in alledaagse spreeksituaties op dit moment?

Please put the slider on the line on this 9-point scale with 1 = extremely satisfied and 9 = extremely dissatisfied / Veuillez mettre le curseur sur la ligne avec 1 = extrêmement satisfait et 9 = extrêmement mécontent/ Zet de slider alstublieft op de lijn met 1 = extreem tevreden en 9 = extreem ontevreden.

|                        |                           |
|------------------------|---------------------------|
| Extremely
satisfied | Extremely
dissatisfied |
|------------------------|---------------------------|

## STUTTERING DETAILS/DETAILS DU BÉGALEMENT/GEGEVENS OVER HET STOTTEREN

- What was the onset of the stuttering (date or period)/Quand est-ce que le bégaiement apparaît (date ou période)/ Wanneer was de onset van het stotteren:.... (months/mois/maand) ..... (year/année/jaar)

- Time since onset/ Temps écoulé depuis l'apparition du bégaiement / Periode sinds de onset van het stotteren  
=
  
- Description (by the parent) of the stuttering/ Description (par le parent) du bégaiement tel qu'il était au moment de son apparition/ Beschrijving (door de ouder) van het stotteren bij onset:  
More than one can apply/ Plus qu'une peut être présent/ Meer dan één kan aanwezig zijn:
  - Repetitions/Répétitions/Herhalingen
  - Audible prolongations/Prolongation audibles/Hoorbare verlengingen
  - Prolongations without audible airflow/Prolongations silencieuses, blocades/Niet hoorbare fixaties/blokkades
  - Reactive behaviour/Comportement associé/Reactief gedrag:
  - Tension (waar, hoe)/Tension (où, comment)/Spanning (waar, hoe):
  - Other fighting behaviour/Autre comportement de forçage/Ander vechtgedrag:
  - Avoiding behaviour/Comportement d'évitement/Vermijdingsgedrag:
  - Other observable behaviour (Start behaviour, postponing behaviour, other):  
 Autre comportement observable pour aider au démarrage des mots, pour retarder la prononciation d'un mot, etc.):  
 Ander observeerbaar gedrag (startgedrag, uitstelgedrag, ander):
  - Non-verbal signs/Signes non-verbaux/Non verbale tekenen: Explain/Expliquez/Leg uit: .....
  - Verbal signs (Child formulated a concern)/ Signes verbaux (L'enfant formulait une préoccupation. / Verbale tekenen (Kind formuleerde een probleem). Explain/Expliquez/Leg uit: .....
  
- Evolution since onset/Evolution depuis le début/Evolutie sinds onset:
  - Gradual increase of stuttering frequency and severity/ Augmentation graduelle de la fréquence et de la gravité du bégaiement/ Geleidelijke toename stotterfrequentie en -ernst:
  - Cyclic but with increased frequency and increased tension, physical and emotional reactions/ Cyclique mais la fréquence et la gravité augmentent avec chaque épisode (tension, réponses physiques et émotionnelles)/ Cyclisch maar met toenemende frequentie en spanning, en met fysieke en emotionele reacties
  - Cyclic but with same frequency and severity, it stays the same/ Cyclique mais avec la même gravité et la même fréquence dans chaque épisode/ Cyclisch maar met dezelfde frequentie en ernst, het blijft hetzelfde
  
- When does the stuttering gets more severe?  
 Quand le bégaiement s'aggrave-t-il?  
 Wanneer is het stotteren ernstiger?
  
- Has the urge to speak decreased since onset? Yes/No. Ask examples.

Le besoin de parler, a-t-elle diminué? Oui/Non. *Demander des exemples.*

Is de drang om te spreken verminderd sinds onset? Ja/Nee. *Vraag naar voorbeelden.*

- Is the urge to speak the same since onset? Yes/No. *Ask for examples.*

L'envie de parler, est-elle restée la même qu'avant? Oui/Non. *Demande des exemples.*

Is de drang om te spreken hetzelfde sinds onset? Ja/Nee. *Vraag naar voorbeelden.*

- Are there reactions towards the stuttering from the child, parent(s) or others? Yes/No. *Ask for examples.*

Y a-t-il des réactions par rapport au bégaiement de la part de l'enfant, des parent(s) ou autres? Oui/Non.

Demander des exemples.

Zijn er reacties op het stotteren door het kind, ouder(s) of anderen? Ja/Nee. *Vraag naar voorbeelden.*

- How does the child respond?

Comment réagit l'enfant?

Hoe reageert uw kind?

- How do you respond?

Comment réagissez-vous?

Hoe reageert u?

- How do you try to help?

Comment essayez-vous d'aider votre enfant?

Hoe helpt u?

- How do the siblings respond (how do they try to help)?

Comment réagissent les frères/les sœurs (comment aident-ils)?

Hoe reageren de broers/zussen (hoe helpen ze)?

- How do the grandparents respond (how do they try to help)?

Comment les grands-parents réagissent-ils (comment aident-ils)?

Hoe reageren de grootouders (hoe helpen ze)?

- How do peers respond (how do they try to help)?

Comment réagissent les petits amis (comment aident-ils)?

Hoe reageren leeftijdsgenootjes (hoe helpen ze)?

- Others?

Autres?

Anderen?

- Has your child received stuttering treatment before? Yes/No. If yes, please explain.

Votre enfant a-t-il déjà reçu un traitement contre le bégaiement ? Si oui, pouvez-vous expliquer?

Werd uw kind reeds behandeld voor stotteren? Indien wel, kan u dit uitleggen?

- Family history of stuttering/Hérédité du bégaiement/Familiaal voorkomen van stotteren

- Present-Not present/Présente -Pas présente/Komt voor-Komt niet voor.
- Relationship with that person/Relation avec cette personne/Relatie met deze persoon:
- Recovery of stuttering? Yes-No/ Récupération? Oui-Non/Herstel? Ja-Nee.
- Did this relative receive treatment? Yes-No. Duration? Type of treatment?  
 Cette personne a-t-elle suivi une prise en charge? Oui-Non. Durée? Type de prise en charge?  
 Werd deze persoon behandeld? Ja-Nee. Duur? Soort behandeling?

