### 8.8.1 *Screening:*

During the screening, the SLT checks the eligibility of the PCWS. The SLT determines the presence of stuttering. The SLT also records the medical history of the PCWS with the focus on the stuttering history (stuttering onset, time since onset, family history of stuttering, ...) and uses the Anamnesis form (Appendix 3) to do this. The SLT informs the parent(s) of the PCWS about the nature and purpose of TreatPaCS and provides him/her with a consent form.

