### **8.8.2 *Period of active monitoring (optional)***

A period of active monitoring can be installed if the stuttering shows signs of spontaneous recovery (e.g., decrease of stuttering severity since onset). A list of potential signs will be provided in the TreatPaCS manual (SLT site file). The SLT records the start and end date and the type of information that parents record during the period of active monitoring.

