#### *11.3.5 Other statistical considerations.*

We will explore if we can find a profile of children more successful to one of the programs, possible factors that will be studied are gender, co-morbidities, age at assessment, family history of stuttering, family history of recovery of stuttering, onset data (gradual/sudden, time since onset, progress since onset), answers to the ISPP-questionnaire, baseline stuttering severity assessment (%SS and SR), parent profile and temperament (CBQ-short version). This will be studied in a linear regression model with %SS at 18 months as outcome and in a logistic regression model with success defined as  $<1\%$  SS and  $SR \leq 1$  as a binary outcome.

We will explore the agreement between the video samples recorded at home and those recorded during the sessions for %SS and SR.

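### The printed anamnesis form has no item for sudden or gradual onset and no improving answer for the course since onset, yet both are planned exploratory predictors

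*Protocol*

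**What the plan says.** Sections 4.3.3 and 11.3.5 of the protocol announce an exploratory search for profiles of children who respond better to one of the programmes. Both list the same three onset variables; section 11.3.5 has "onset data (gradual/sudden, time since onset, progress since onset), answers to the ISPP-questionnaire". These are candidates for a linear model of %SS at 18 months and a logistic model of success.

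Section 8.8.1 names the tool for the stuttering history: the therapist records "stuttering onset, time since onset, family history of stuttering, ...) and uses the Anamnesis form (Appendix 3) to do this". The schedule of measurements (Figure 3) has an anamnesis row and no other onset instrument.

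In the stuttering details part of Appendix 3, the onset question reads "What was the onset of the stuttering (date or period", with fields for month and year. It is followed by time since onset and a tick list of behaviours seen at onset. The item on evolution since onset then gives three answers:

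- "Gradual increase of stuttering frequency and severity"
- "Cyclic but with increased frequency and increased tension, physical and emotional reactions"
- "Cyclic but with same frequency and severity, it stays the same"

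Section 8.8.2 says: "A period of active monitoring can be installed if the stuttering shows signs of spontaneous recovery (e.g., decrease of stuttering severity since onset". Section 8.1.2 makes the course since onset one of the grounds on which the therapist decides whether to monitor, treat or do neither. Section 11.3.1 compares the arms at baseline on a stuttering onset questionnaire, which is not identified or appended under that name.

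**The concern.** The analysis sections ask for variables that the collection form does not deliver. Nobody is asked whether onset was sudden or gradual. The question on the course since onset runs from worsening to unchanged and stops there, so the answer the protocol itself links to natural recovery cannot be given.

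The two gaps differ in kind. The onset-type gap applies to every child. The evolution gap is selective: it falls on children who were improving, and to a lesser degree on those who were stable without cycles. At stake is whether the profile search in sections 4.3.3 and 11.3.5 can use two of its named onset predictors and, if the form is the onset questionnaire of section 11.3.1, whether the baseline table describes the arms correctly on this point. An analysis plan written later cannot recover a variable that was never collected.

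**Working it through.** There is no figure in the plan to reproduce, so the check sets the planned predictors beside the form.

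| Planned predictor (4.3.3, 11.3.5) | Item on the printed form (Appendix 3) | Can it be coded? |
|---|---|---|
| Time since onset | Month and year of onset; time since onset | Yes |
| Onset type, gradual or sudden | None | No, for any child |
| Progress since onset | Evolution since onset, three answers | Only for children who worsened, or who cycled without change |

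**Onset type.** The word gradual does appear on the form, in "Gradual increase of stuttering frequency and severity", but it describes the later course. A child with a sudden onset can worsen gradually afterwards, so this answer cannot stand in for onset type. The tick list of behaviours at onset says what the stuttering looked like, not how quickly it began.

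**Progress since onset.** Counting answers by direction: worsening 2, unchanged 1 (cyclic only), improving 0, stable without cycles 0, other 0. The French and Dutch texts give the same three answers, so a translation slip is unlikely. Elsewhere the same form covers every direction (slower, same pace or faster, for language and motor development) and offers an open answer (family circumstances, day care, monitoring). The omission is therefore particular to this item.

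**What happens to an improving child.** There are two routes:

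1. The item is left blank. The value is then missing because of what it would have been. Imputation cannot produce a category that was never recorded for anyone.
2. The child is coded as unchanged or worsening. That category then mixes two courses, and its coefficient in the linear or logistic model no longer means what its label says.

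**Reach.** The covariates listed for the primary weighting model in section 11.3.2 are gender, age, comorbidities, family history and recovery, parent profile, baseline %SS and SR, and temperament. The list is given as examples, but neither onset variable is in it. Neither is named among the covariates in section 11.3.3. What remains is the exploratory models and, conditionally, the descriptive summary in section 11.3.1.

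**The case against.** The strongest reply is that the eCRF is not shown. Section 12.1 has the chief investigator and the trial statistician validate it so that it holds the data points the analysis needs, and the onset questionnaire of section 11.3.1 may be a separate instrument. A field outside the printed form therefore cannot be excluded, and that part stands: a reader might infer that onset type is missing for 249 of 249 children, but the documents do not prove it. They do make such a field unlikely. Section 8.6 has the therapist enter the answers to this form into the eCRF, and section 13 requires the baseline data from it to be traceable to source documents. A field with no question behind it would have no defined source.

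A second reply is that children under active monitoring have severity information recorded separately (section 8.6 and the last part of Appendix 3). That helps for recent change in those children only, over at most three months. It is not progress since onset.

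A third is that the use is exploratory. That is right, and it limits the weight of the point. Three stronger readings should be set aside:

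- A reader might take the 74% recovery in section 1 as the size of the omitted category. That figure covers four years after onset, not improvement at intake. The same section cites 5 of 84 children (6%) recovering at 12 to 17 months, and children for whom treatment is not started are not invited. The share of enrolled children who were improving is not given.
- A reader might see progress since onset as the main marker separating natural recovery from treatment effect. No section gives it that role. All three arms are treated and randomised, so natural recovery is expected to be similar across them.
- A reader might think both gaps fall on children likely to recover. Only the evolution item fails selectively.

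**Conclusion.** The point holds as a mismatch between planned analysis and printed form. Of three named onset predictors, one can be derived, one has no item, and one has no improving answer. As printed, onset type cannot enter the profile models, and improving children are lost or misclassified on progress since onset.

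The consequence is confined to the exploratory models of sections 4.3.3 and 11.3.5 and, if the Anamnesis form is the onset questionnaire, to the baseline summary of section 11.3.1. The primary non-inferiority comparison is not directly affected, nor is the sample size.

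This rests on two assumptions: that the eCRF mirrors Appendix 3, and that no separate onset instrument exists. The number of improving children among those enrolled is unknown, so the extent of misclassification cannot be quantified. The correction is worth making because it is cheap and because onset history becomes harder to recover with time.

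**What to change.** In Appendix 3 and the eCRF, in all three languages:

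- Add one item on onset: *sudden / gradual / not known*.
- Add four answers to the evolution item: *gradual decrease*; *cyclic with decreasing frequency or severity*; *stable, not cyclic*; *other*.
- State in section 11.3.1 which items make up the stuttering onset questionnaire.

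For children already enrolled, use only information documented before the allocation was revealed, and otherwise code the item as missing. If parents are asked later, flag the answer as recall and examine it in a sensitivity analysis. Simply completing both items from the therapist's file would be unsound. The onset history in that file is gathered with this same form, and the therapists know the allocation (section 8.4) and may have seen the response. Section 8.6 also has the form entered after the baseline session, so the date that matters is that of the notes, not of the data entry.

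If onset type cannot be collected, remove it from the lists in sections 4.3.3 and 11.3.5.

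The cost is one extra question, a few answer options and some missing values in early enrollees. No new assessment is needed.
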